#### Procedures

At routine scoliosis clinic visits a nurse will determine eligibility and randomize participants to the observation (control) or the Schroth

exercise group. Outcomes will be measured at baseline, 3 and 6 months. Primary outcomes include baseline and 6-month radiographic curve measurements and SRS-22 questionnaire. Secondary outcomes will include postural measures (Surface Topography), Global Rating of Change (GRC), Self-efficacy questionnaire, pain, and back muscle endurance. Predictors of success will be collected at baseline.

Controls will receive the current standard of treatment for 6 months (Observation or brace prescribed as per SRS guidelines). Patients treated with Schroth exercises will participate weekly in supervised Schroth exercises and complete a daily home program for 6 months. The baseline and 6-month exam will be completed within 2 weeks of a scoliosis clinic visit with a follow-up at 3 months. After 6 months, controls will crossover to the treatment group. After 12 months and for every scoliosis visit afterwards until discharge, we will also extract the radiograph and SRS-22 questionnaire from the Edmonton Scoliosis records

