#### Questionnaires:

*Demographic/History-* Socio-demographics, symptoms history and modifying factors will be self-reported.

*Pain rating and diagram-* A numeric scale from 0 (no pain) to 10 (worst imaginable pain) will assess current, best, worst intensity in the last 24 hours. A diagram will assess location of symptoms.

*Scoliosis-Research-Society questionnaire (SRS-22r)-* The SRS-22r assesses quality-of-life within 5 domains: function, pain, self-image, mental health (5 questions each), and satisfaction (2 questions).

*3D Physical activity recall (3DPAR)*- quantifies habitual physical activity chosen among 55 activities listed, and their intensities for blocks of 30-min over 3 days. The 3DPAR score is determined using the metabolic equivalent (MET) levels.

*Spinal Appearance Questionnaire*- includes 21 items pertaining to the severity of the deformity within 9 domains (Trunk shift, Waist, Kyphosis, Prominence, Chest, Shoulders, General and Curve) .

*Self-efficacy* – measures self-efficacy for overcoming barriers to physical activity using 8 items rated from 1 (Disagree a lot) to 5 (Agree a lot).

*Global Rating of Change (GRC)*- A 15-point GRC ranging from –7 (very great deal worse) to +7 (very great deal better) will be used.

Physical Exam(Appendix E): An physiotherapist blind to groupings will assess curve type and hip range-of-motion in flexion, extension, internal rotation, the straight-leg-raise and FABERE tests. Sorensen's test will assess back extensor muscle endurance. Lumbar (inclinometers at L5/S1 and T12/L1) and thoracic (C7/T1 and T12/L1) spinal range-of-motion will be recorded: lumbar flexion, extension and side flexions. Scoliometer will record asymmetry during the Adam bending test.

Radiographs- Standing postero-anterior radiographs in a positioning frame at baseline, 6 and 12 months and from every scoliosis clinic visits until discharge will be used to measure the Cobb angle, rotations, apex translation. An experienced evaluator blind to group assignment will extract measures.

Surface topography(ST) – An experienced evaluator will operate four scanners and use a positioning frame to scan torso shape. The following ST parameters will be extracted by digitizing 15 points on de-identified scans (blinding): cosmetic score, shoulder angle, scapula angle, waist asymmetry, trunk rotation, kyphotic and lumbar indices.

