## **Analyses:**

Intention to treat (by carrying forward last known value) linear mixedmodel analyses will be used to assess differences in group changes from baseline, to 3 and 6-month while adjusting for covariates. Separate analyses will be conducted for each outcome. To screen for variables associated with each of the outcomes variables, we will use univariate linear mixed models and include all relevant covariates (age, time since menarche, apex levels, physical activity, self-efficacy, and bracing compliance may have associations with risk of progression). Multiple linear mixed models will be tested including covariables found significant at  $P=0.20$  in the univariate analysis, and after screening for multicollinearity. Results will be presented as effect sizes with confidence intervals and one-sided P-values. Statistical analyses will be performed using SAS version 9.1.

For subjects initially in the control group later completing 6 months of exercises, intention to treat linear mixed-model analyses will be used to assess differences between the two periods (standard care vs standard care + Schroth) in changes from baseline, to 3 and 6-month, while adjusting for covariates. Screening for covariates will be done as described above. In this model, treatment period is a dependent factor.

To determine if exercises effects are maintained at 12 months and discharge exams, linear mixed- model analyses will also be used to quantify the effect sizes corresponding to changes from 6 to 12 months and to discharge by combining data from all patients after participating in the exercise program.

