### **3.0 Describe procedures, treatment, or activities that are above or in addition to standard practices in this study area (eg. extra medical or health-related procedures, curriculum enhancements, extra follow-up, etc):**

SRS-22 and Spinal appearance questionnaires, surface topography and radiograph scanning (which will be extracted from the hospital database) are standard practices at the specialized Scoliosis Clinic. The data routinely collected at scoliosis clinic visits will be used in the study. Clinics are routinely scheduled every 6 months for patients meeting the eligibility criteria in our study.

Our 3 months assessment is additional to the routine visits. Some tests at baseline, 3 and 6 months are additional to routine visits and all exercise treatments are additional to routine visits.

Participating in the study requires completing tests and questionnaires in addition to usual procedures. Physical examination at baseline, 3 and 6 months including range of motion of back and lower extremity are not current practice. The following questionnaires completed at baseline, 3 and 6 months are extra procedures, too: Demographic/History, Pain rating and diagram, 3D Physical activity recall, Self-efficacy and Global Rating of

Change.

All exercise visits are additional to routine scoliosis visits.

- 4.0 If the proposed research is above minimal risk and is not funded via a competitive peer review grant or industry-sponsored clinical trial, the REB will require evidence of scientific review. Provide information about the review process and its results if appropriate.**  
 Glenrose Hospital Foundation, Clinical Research Grant Review Committee (completed)  
 Scoliosis Research Society, Small Exploratory Grant Review Committee (completed 2009 and 2010)  
 Women's and Children Health Research Institute, CIHR Pre-review Process (completed)  
 SickKids Foundation New Investigator Review committee (awarded in 2013, completed also in 2010)

- 5.0 For clinical trials, describe any sub-studies associated with this Protocol.**

ID: Pro00043397

Pro00043397

Status: Approved

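### The Global Rating of Change is already a change score, but the plan collects it at baseline and analyses it as change from baseline (minor)

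*Protocol*

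**What the plan says.** Four statements in Protocol section 2.1 bear on the GRC.

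- **Role and general schedule (Procedures).** "Secondary outcomes will include postural measures (Surface Topography), Global Rating of Change (GRC), Self-efficacy questionnaire, pain, and back muscle endurance". The same paragraph says: "Outcomes will be measured at baseline, 3 and 6 months".
- **Scale (Questionnaires).** The GRC has 15 points, and −7 to +7 is labelled "very great deal worse) to +7 (very great deal better) will be used". The period over which the patient is to judge the change is not given.
- **Baseline collection (item 3.0, procedures beyond standard practice).** "The following questionnaires completed at baseline, 3 and 6 months are extra procedures"; the list that follows names the GRC as its last item.
- **Analysis (Analyses).** Mixed models are to "assess differences in group changes from baseline, to 3 and 6-month while adjusting for covariates. Separate analyses will be conducted for each outcome". Intention to treat is defined there as carrying the last known value forward. The comparison of the two periods within the original controls is likewise framed as changes from baseline. The GRC is not excepted from any of this.

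**The concern.** Most outcomes here are states: an angle, a pain score, a holding time. For these, change from baseline is the natural measure. A GRC answer is not a state, because the patient has already done the subtraction. Taking a second difference gives a change in a change rating.

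At baseline the patient has no time in the trial to judge, so whatever she answers concerns some earlier, unspecified interval. If she rates −3 at entry because she had been getting worse, and 0 at 6 months because she has been stable, the planned score is +3. If she rates +3 at entry and +3 at 6 months, the score is 0 although she reports improvement on study.

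At stake is what the reported GRC result means, and possibly how precisely it is estimated. The primary outcomes (radiographic curve and SRS-22) are states and are not touched.

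**Working it through.** **1. Does the rule reach the GRC?** It is a named secondary outcome; it is named in the list of forms completed at baseline; each outcome is analysed as change from baseline; no exception is written. Followed as written, the plan subtracts the baseline GRC. Using a mixed model does not alter this, since its group contrast in change from baseline is still follow-up minus baseline, compared between arms.

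**2. Is the between-arm contrast biased?** Difference in mean change = (difference in mean follow-up rating) − (difference in mean baseline rating). Randomisation makes the second term zero in expectation, so there is no systematic bias between arms.

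**3. Carry-forward.** A participant with only a baseline GRC has that rating entered at 3 and 6 months. Her change is then zero by construction, and her entered follow-up ratings were given before any treatment.

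**4. The plan's own figure.** Inputs from section 4.2 item 5.0: effect size 0.31, 80% power, one-sided alpha 0.05.

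- n per arm = 2(1.645 + 0.842)² / 0.31² = 128.7, so 129. The stated figure reproduces.
- Power at n = 129: Φ(0.31 × √(129/2) − 1.645) = Φ(0.845) = 80.1%.

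**5. Effect of subtraction on precision.** Let k be the baseline SD divided by the follow-up SD, and rho the correlation of the two ratings. The Protocol gives neither, so both are assumptions. It is also an assumption that the 0.31 SD applies to the direct GRC rating, since section 4.2 states it for change in outcomes generally.

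SD of the difference, in follow-up SDs: s = √(1 + k² − 2·rho·k). Effect after subtraction = 0.31/s. Power = Φ((0.31/s) × √(129/2) − 1.645).

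| k | rho | s² | Effect (SD) | Power |
|---|---|---|---|---|
| 0 (all rate 0 at baseline) | – | 1.00 | 0.310 | 80.1% |
| 1 | 0 | 2.00 | 0.219 | 54.6% |
| 1 | 0.25 | 1.50 | 0.253 | 65.1% |
| 0.5 | 0 | 1.25 | 0.277 | 72.0% |
| 1 | 0.5 | 1.00 | 0.310 | 80.1% |
| 0.5 | 0.5 | 0.75 | 0.358 | 89.1% |

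Subtraction costs power when rho < k/2, is neutral at rho = k/2 and gains above it.

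**6. Within-control comparison.** Randomisation does not protect this one. The Protocol names no separate baseline exam for the second period. If the 6-month rating serves as that baseline (an assumption), a control who rates 0 at entry and +2 at the end of each period scores +2 for standard care and 0 for the exercise period, though she reported the same change in both.

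**The case against.** The Analyses sentence is generic and never mentions the GRC. It is not exact for every outcome either: section 2.1 places radiographs at baseline and 6 months, without a 3-month film. Item 3.0 answers an ethics-form question about participant burden. A SAP, not shown here, could handle the GRC separately. This tempers certainty about what will be done. It does not remove the point, because the baseline collection and the change-from-baseline rule are both written down, and together they give the wrong measure for this scale.

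A reader might infer three stronger things that the Protocol does not support.

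- **That the baseline rating is meaningless.** With no reference time stated, it could refer, for example, to the interval since the last routine clinic visit. That would have meaning, though not as change in the trial.
- **That the subtraction biases the comparison of arms.** It does not in expectation (step 2).
- **That it costs a known amount of power.** The 55% result needs equal SDs and zero correlation. Other assumed values give no loss, or a gain to 89%.

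Two further objections stand. No responder or threshold analysis of the GRC is described, so odd individual scores matter only for reading the result. Carry-forward from baseline should concern few participants, as section 4.2 reports pilot dropout below 10%.

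**Conclusion.** The point holds as a minor one. As written, the plan takes a change-from-baseline of a scale that already records change, so the GRC result would not express perceived change on study, and a pre-treatment rating can stand in for a missing follow-up rating. The text alone supports this.

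The size is limited: one secondary outcome, no expected bias between arms, no effect on the primary outcomes or the sample size. The effect on precision cannot be fixed from the Protocol. For an assumed 0.31 SD difference in the direct rating, power after subtraction is between 55% and 89% over the range examined, against 80% without it. A distortion of the within-control comparison follows only if the 6-month rating is used as the second-period baseline.

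**What to change.** In the Analyses text, exempt the GRC from the change-from-baseline rule and from carry-forward of a baseline rating. Compare the 3- and 6-month ratings directly between arms, and do not use baseline GRCs already collected.

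State the reference time as the start of the current treatment period: enrolment for the randomised comparison, and the start of the exercise period for controls who have crossed over. A single anchor at study entry would not do, because a crossed-over control's second-period rating would then include her standard-care months. In the within-control analysis, compare the end-of-period ratings directly. Where ratings were already collected with another anchor, report that anchor.

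The analysis change costs a sentence or two. Section 4.5 says enrolment is complete, so dropping the form at baseline would now achieve little, and the anchor can be changed only for ratings still to come.

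### Bracing compliance, a post-randomisation variable, can enter the intention-to-treat model; self-efficacy and physical activity are not restricted to baseline; and covariates are selected from the outcome data at P=0.20

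*Protocol*

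**What the plan says.** Protocol 2.1, Analyses, describes linear mixed models, labelled intention to treat, that "assess differences in group changes from baseline, to 3 and 6-month while adjusting for covariates". "Separate analyses will be conducted for each outcome", and the screening rule applies to each one. Univariate models will "include all relevant covariates (age, time since menarche, apex levels, physical activity, self-efficacy, and bracing compliance may have associations with risk of progression"). Then "Multiple linear mixed models will be tested including covariables found significant at" P=0.20 "in the univariate analysis, and after screening for multicollinearity". No measurement time is given for any candidate, and no covariate is forced into the model.

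Three other statements bear on this:

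- 2.1, Procedures, outcomes: "Secondary outcomes will include postural measures (Surface Topography), Global Rating of Change (GRC), Self-efficacy questionnaire, pain, and back muscle endurance".
- 2.1, Procedures, timing of predictors: "Predictors of success will be collected at baseline".
- 2.1, item 3.0, timing of questionnaires: "The following questionnaires completed at baseline, 3 and 6 months are extra procedures, too: Demographic/History, Pain rating and diagram, 3D Physical activity recall, Self-efficacy" and the Global Rating of Change.

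Patients may enter with or without a brace (2.1, Subjects). Item 4.0 of section 3.1 says that patients who progress far enough to meet bracing criteria are referred to their surgeon for treatment.

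**The concern.** An intention-to-treat comparison estimates the whole effect of being allocated to exercise. Adjusting for a variable that allocation can change takes out whatever part of the effect passes through it, and can add bias if the variable also responds to the outcome.

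Bracing compliance during follow-up is exposed to both problems. The exercise arm has five individual sessions and then weekly therapist contact that controls lack, so allocation could alter brace wear. A brace may also be started because the curve has progressed, so wear can follow from the primary outcome. An unbraced patient has no compliance value: left missing, a standard mixed model drops her; coded zero, the variable merges not prescribed with not worn. The Protocol chooses neither.

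Self-efficacy is a candidate covariate for every outcome and is itself an outcome, so its own analysis could become circular. For the other outcomes, self-efficacy and physical activity are harmless at baseline values and carry the same risk as compliance at 3- or 6-month values.

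The primary adjusted model is also unknown until the outcome data have been screened. Baseline Cobb angle, Risser sign, brace prescription at entry and site are neither named in the Analyses paragraph nor forced in.

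**Working it through.** **1. Each named candidate against its timing in the Protocol**

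| Candidate | Measured when | Can allocation affect it? |
|---|---|---|
| Age, time since menarche, apex levels | time point not stated | baseline values: no |
| Physical activity | baseline, 3, 6 months | only if follow-up values are used |
| Self-efficacy | baseline, 3, 6 months; also an outcome | only if follow-up values are used |
| Bracing compliance | no measure described | yes, if it is compliance during the trial |

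**2. The Protocol's own sample size.** Inputs (4.2, item 5.0): effect size 0.31, one-sided alpha 0.05, power 80%, 129 per group including 25 per group from the pilot.

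n per group = 2 × (1.645 + 0.842)² / 0.31² = 128.7, so 129. This reproduces.

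Power = Φ(0.31 × √(129/2) − 1.645) = Φ(0.845) = 80.1%.

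**3. What adjustment could do.** Let s be the share of the effect that runs through an adjusted post-baseline variable. The Protocol gives no value for s; the range is assumed. Adjusted effect = 0.31 × (1 − s), and power = Φ(adjusted effect × √64.5 − 1.645).

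| s | Adjusted effect | Power |
|---|---|---|
| 0 | 0.310 | 80% |
| 10% | 0.279 | 72% |
| 20% | 0.248 | 64% |
| 30% | 0.217 | 54% |
| 50% | 0.155 | 35% |

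A simulation of 4,000 trials per row that included the P<0.20 screen gave adjusted effects of 0.280, 0.248, 0.216 and 0.153 for the last four rows. It kept the variable in 67%, 95%, 99.7% and 100% of trials, so the screen gives little protection.

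**4. Compliance exists only in braced patients, and the sign is open.** Suppose a fraction p is braced, compliance shifts by 0.3 SD in the exercise arm, and its slope on the outcome is 0.3 (all assumed). Adjusted effect = 0.31 − p × 0.3 × 0.3. For p = 30%, 50% and 70% this is 0.283, 0.265 and 0.247. If exercisers wear the brace less, the sign flips: 0.337, 0.355 and 0.373.

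**5. The screen by itself.** With N = 258 and a two-sided P=0.20 criterion (Fisher z), a covariate correlated 0.05, 0.10, 0.15, 0.20 or 0.30 with the outcome is kept in 33%, 63%, 87%, 97.5% or about 100% of trials. If all six named candidates were independent noise, 6 × 0.20 = 1.2 would be kept on average, and at least one in 1 − 0.8⁶ = 74% of trials.

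With baseline candidates only, 6,000 simulated trials per setting gave a one-sided type I error of 5.2% with six null candidates and 4.8% with assumed slopes of 0.3, 0.2 and 0.1 on three of them. The mean estimate was 0.307 for a true 0.31 in both.

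**6. A fixed baseline set.** The full 0.31 is retained. With residual SD √(1 − r²), power is 80.1%, 81.5%, 83.3% and 85.8% for an assumed joint correlation r with the outcome of 0, 0.2, 0.3 and 0.4.

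**The case against.** The Procedures paragraph says predictors are collected at baseline, and the Analyses paragraph introduces the candidates as factors linked to risk of progression. A reader might infer from the repeated questionnaires that self-efficacy and physical activity enter at follow-up values. The Protocol does not say so, and the sentence on predictors leans the other way. That objection stands: for these two the defect is an unfixed time point. It helps less with compliance, which could be a baseline measure only for patients already braced at entry.

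A reader might also infer that the screen leaves strong baseline predictors to chance, or that it inflates type I error. Neither is supported. At this sample size a listed predictor correlated 0.20 or more with the outcome is nearly always kept, and with baseline candidates the simulations show no visible cost in error rate or bias. What remains is a pre-specification weakness: the model can differ by outcome and is settled only after outcomes are seen.

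The candidate list may be illustrative rather than closed, brace treatment is called a potential predictor elsewhere (4.2, item 2.0), and an analysis of change already uses the baseline Cobb angle. The fair statement is therefore that the key baseline variables are not named as covariates or forced in, not that they are excluded.

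Finally, the mediated share is assumed. That too stands, and it limits what can be said about size.

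**Conclusion.** The point holds in a limited form. The Analyses paragraph itself names bracing compliance for an intention-to-treat model, lists an outcome as a covariate for every outcome, fixes no time point, and sets a data-driven selection rule. These are stated rules, not details left to a later plan.

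It would go too far to say that the primary estimate is biased, or biased towards no effect. That requires allocation to change an adjusted variable that is also related to the outcome, and the Protocol gives no figure for either link. The falls to about 0.28 to 0.16 in effect and 72% to 35% in power are illustrations for an assumed 10% to 50% mediated share. They treat the primary analysis as a two-group comparison of change and a single adjusted variable as present in everyone; with compliance confined to braced patients the distortion can be smaller, and it can run in the opposite direction. This should be fixed before analysis because it affects the primary estimate and costs little, but it is not shown to have done damage.

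**What to change.** In Protocol 2.1, Analyses:

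- Remove bracing compliance from the efficacy model. Report it, where recorded, descriptively by arm or in a separate exploratory analysis. The Protocol describes no measure of brace wear (the logbook covers the exercises), so state how it is obtained.
- State that physical activity and self-efficacy, if used at all, enter only at their baseline values.
- Replace the P=0.20 screen with one baseline covariate set fixed in advance: for example the baseline value of the outcome, Risser sign, age, brace prescription at entry and site. Other prespecified baseline sets would serve equally well.
- Apply the same rule to the analysis of controls who cross over, which reuses the screen.

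This is a change of wording, with no new patients and no new visits. The small downside is that a fixed set may carry a weak covariate, which with 258 patients costs very little precision.

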**4.0**

**If this application is closely linked to research previously approved by one of the University of Alberta REBs or has already received ethics approval from an external ethics review board(s), provide the study number, REB name or other identifying information. Attach any external REB application and approval letter in the Documentation Section – Other Documents.**

The present study is an extension to multiple site of the pilot SETS study approved by HREB as Pro00011552 with the exception that we do not plan to collect blood samples at this point in the multicenter study.

- The surface topography assessment protocol has been used in the study: "Full Torso Surface Topography for Scoliosis" (PRO00006268) and in the study: "360 Degrees Surface Topography Parameters (Norms)" (PRO00003600)
- The use of SRS-22 Questionnaire was approved in all of the above mentioned studies.
- The physical assessment has been approved in the PRO00006957 and

in the PRO00003600 studies.

- The radiograph analyses have been approved in the PRO00006268 study.

ID: Pro00043397

Pro00043397

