### **Methods**

#### Subjects

Female patients with AIS, JIS, or syringomyelia without chiari (n=208) will be recruited in Edmonton, Calgary and Montréal. Inclusion criteria are: (1) curves 10°-45°, (2) age 10-16 (3) All Schroth curve types (3c, 3cp, 4c and 4cp), (4) treated with or without brace (5) living within 1 hour of the study site and (6) with Risser sign less than or equal to 3. Those planning or post-surgery will be excluded.

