 -Patients with curves over 30° have a risk of progression beyond skeletal maturity. Schroth exercises are recommended for all curve sizes.

(4) age 10-16  
 -Patients are treated between the ages of 10-18 at the Edmonton Scoliosis Clinic. Inclusion of patients over the age of 10 allows for comprehension of Schroth exercise program. Limiting upper limit of age range to 16 increases the likelihood that the patients are skeletally immature and therefore still truly at risk of progression. Patients having reached the skeletal maturity are simply given a recommendation to exercises but the prescription would be deemed optional in most cases.

The SickKids reviewers requested we enroll skeletally immature patients only.

- (5) ability to travel to study sites at least weekly.
  - To ensure that we can assess the efficacy of the proposed exercise protocol we require the participant to attend weekly exercise sessions at the study sites. This will ensure feasibility of the trial with opportunity for maximal compliance.

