## 5.0 Justification for sample size:

Primary and secondary aim 1: A sample of 129 subjects per group will be sufficient to detect a 0.31 effect size when comparing the change in outcomes between the exercise and control groups with 80% power using a unilateral test and an alpha of 0.05 (104 Schroth and 104 controls in this study + 25 Schroth and 25 controls in the pilot allows a total of 129 per group). We anticipate >80% completion rate based on published data and because the pilot dropout rate was <10%. Our per-protocol sample may drop slightly however, we are planning intent to treat analyses where we will carry-forward the last known observation from our participants.

A unilateral hypothesis is justified, for this superiority trial, by positive published data and our pilot data. The pilot effect size for the Cobb angle was 0.32 and many secondary outcomes had effect sizes exceeding what we are powered to detect as significant. A trial conclusive in favour of exercises would have a significant impact in America. A trial failing to demonstrate positive results would have less impact as Schroth exercises are not currently prescribed. We believe that a 0.32 effect size is clinically important, feasible, and would justify implementing a Schroth program. The trial duration is relatively short which justifies aiming to detect a small effect size (0.2-0.5) .

It would be inadequate to power the trial to detect too small an effect size as patients and families will likely demand evidence of clinically important effects before committing efforts and time required of Schroth exercise programs. For the secondary aim comparing the results of subjects in the control group who first complete 6 months as controls to their results after completing 6 months of Schroth exercises, an effect size of 0.27 (n=106) could be detected as significant with a power of 0.80, an alpha of 0.05 with a unilateral test.

ID: Pro00043397

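### Site and study phase have no protected place in the between-group models, although a three-city trial is pooled with its pilot; the likely cost is a little precision

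*Protocol*

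**What the plan says.** Under Analyses in protocol section 2.1, "linear mixedmodel analyses will be used to assess differences in group changes from baseline, to 3 and 6-month while adjusting for covariates". Candidates are first tested one at a time: the plan will "include all relevant covariates (age, time since menarche, apex levels, physical activity, self-efficacy, and bracing compliance"). Then "Multiple linear mixed models will be tested including covariables found significant at" P=0.20, after a check for multicollinearity. This is done separately for each outcome. Six candidates are named. Site and study phase are not among them, and the protocol does not enter either as a fixed or random effect elsewhere.

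The design has both features. Under Subjects, patients "will be recruited in Edmonton, Calgary and Montréal". The item on linked research in the multi-institution review section states: "The present study is an extension to multiple site of the pilot SETS study". The sample size justification (section 4.2, item 5.0) reaches 129 per group by adding "104 Schroth and 104 controls in this study + 25 Schroth and 25 controls in the pilot". The Analyses text does not mention this pooling. Under Procedures, a clinic nurse randomises; stratification by site is not mentioned.

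Items 4.1 to 4.3 of section 4.2 give 100 participants to recruit, 26 of them controls, and 208 in the entire study. Because item 4.3 asks separately about the whole study, the 100 reads as the local figure.

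**The concern.** Site and study phase are design variables. They describe how the sample was assembled, and one normally fixes them in the model in advance. Here they are not named, and if they were taken to be relevant covariates they would still have to pass a P=0.20 screen. That screen could drop them, or keep them for one outcome and not for another.

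Two things could be at stake. The first is precision: any difference between sites or phases in the change from baseline stays in the residual. The second is bias, but only if the arms draw on sites or phases in different proportions. Phase deserves attention because the power claim rests on the pooling. There is also a hint that the two phases may not be alike: in the inclusion criteria, "The SickKids reviewers requested we enroll skeletally immature patients only".

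**Working it through.** **Inputs from the protocol:** 129 per group, standardised effect 0.31, 80% power, one-sided alpha 0.05; 104:104 in the trial and 25:25 in the pilot; 100 participants with 26 controls (read as local); 208 overall. **Assumed, not in the documents:** the size of any site or phase effect on change.

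**1. The plan's own figure.** n per group = 2(1.645 + 0.842)²/0.31² = 128.7, so 129. This reproduces the plan. Power at 129 per group = Φ(0.31·√(129/2) − 1.645) = 80.1%. The trial's own 104 per group would give 72.3%.

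**2. Phase and bias.** Pilot patients are 25/129 = 19.4% of each arm. Bias = (difference in share between arms) × (phase shift) = 0 × shift = 0. In 40,000 simulated unadjusted one-sided tests with a 0.3 SD phase shift and no treatment effect, the type I error was 4.8%, so it is not inflated.

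**3. Site and bias under 1:1 randomisation.** With a local share of 100/208 = 0.481, the chance difference between arms has SD √(0.481 × 0.519 × 2/104) = 0.069, so 95% limits are ±1.96 × 0.069 = ±0.136. Times an assumed 0.2 SD site shift, this is ±0.027 SD, about ±0.03.

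**4. Precision.** If 0.31 is on the unadjusted SD, adjustment multiplies the SD by √(1 − R²), where R² is the share of variance explained by site and phase:

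| Assumed R² | Power at 129 per group | n per group for 80% |
|---|---|---|
| 0 | 80.1% | 129 |
| 0.5% | 80.3% | 129 |
| 1% | 80.4% | 128 |
| 2% | 80.8% | 127 |
| 5% | 81.8% | 123 |
| 10% | 83.6% | 116 |

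If 0.31 is instead on the within-stratum SD, leaving the terms out inflates the variance from 1 to 1 + v:
- Phase: v = p(1 − p)d² with p = 50/258. Shifts d of 0.2, 0.3 and 0.5 SD give power of 79.9%, 79.6% and 78.7%.
- Three equal sites at −d, 0 and +d: v = 2d²/3. Values of d of 0.2, 0.3 and 0.5 SD give 79.2%, 78.0% and 74.5%.

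**5. The conditional case.** Suppose 26 local controls and 74 local exercisers were real alongside 104:104. Taking the pilot as local, the local site would supply (74 + 25)/129 = 99/129 of exercisers and (26 + 25)/129 = 51/129 of controls, a gap of 48/129 = 0.372. Assumed site shifts in change of 0.1, 0.2 and 0.3 SD would then give biases of 0.037, 0.074 and 0.112 SD, or 12%, 24% and 36% of 0.31.

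The same premise leaves the other sites with 104 − 26 = 78 controls and 104 − 74 = 30 exercisers. That is 74/26 = 2.8:1 towards exercise locally and 78/30 = 2.6:1 towards control elsewhere. The protocol describes no such allocation.

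**The case against.** The strongest reply is that this is silence rather than error. The bracketed list can be read as clinical examples, nothing excludes site or phase, the random effects are not specified, and an analysis plan that is not shown may supply the terms. This stands in part: the protocol does not rule the terms out. But it does fix an entry rule, and under that rule even a variable judged relevant can be screened out. The point is about that rule.

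The second reply is that little is at stake. That largely stands, as steps 2 to 4 show.

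Four stronger readings are tempting, and the documents do not support them:

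- A reader might infer that pooling without a study term compares patients across studies and so confounds the result. Equal arms within each phase rule this out for a phase main effect.
- A reader might take the 26 controls of 100 as evidence of unequal allocation by site. The figure conflicts with 104:104 and would require opposite ratios in different places. A leftover or mistaken form entry is at least as plausible. Computed on the 208 alone, the gap would be 74/104 − 26/104 = 0.462 and the bias 15–45% of 0.31, but that target belongs to the pooled 129 per group, where step 5 applies.
- A reader might suppose that therapists or brace practice differ by site. The protocol does not say so; it describes bracing by common guidelines and exercise prescription by an algorithm and checklist.
- A reader might conclude that eligibility differed between pilot and trial. Remarks about broadened criteria and the funder's request suggest this, but the pilot's criteria are not in the document. That the pilot had a single centre is likewise implied, not stated.

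**Conclusion.** The covariate rule neither names nor protects two design variables of a pooled, three-city comparison, and it should. On the allocation that the sample size section states, the consequence is modest: a gain of about 0.2 to 1.7 power points if site and phase explain 0.5–5% of the variance in change, plus protection against small chance imbalances between sites. A larger loss, to 74.5% power, needs site differences of ±0.5 SD, for which the document gives no basis. Material bias depends wholly on the local control count being real, which is not shown. All site and phase effect sizes here are assumptions. They refer to differences in change from baseline, since stable differences in level cancel.

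**What to change.** Force site and study phase into every between-group model, outside the P=0.20 screen. One simple form is a single factor with the pilot as its own stratum beside the three sites of the multicentre trial. Because the analysis concerns change over time, the terms must act on change. In the repeated-measures model this means including their interactions with time, since main effects alone adjust only the level. If change scores are the outcome, main effects suffice.

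Separately, reconcile the 100 and 26 in items 4.1 and 4.2 of section 4.2 with the 104:104 in item 5.0.

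The cost is small. A four-level factor uses 3 degrees of freedom in a change-score model, and 3 + 3 × 2 = 9 in a model with baseline, 3 and 6 months, from 258 patients. No new data are needed.
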